ACB, Assessment of Concerning Behaviour Scale; ASD, Autism Spectrum Disorders; ICC, Intraclass Correlation Coefficient.

Participants’ questionnaire battery will be presented in HealthTracker™, a web-based platform for online completion (www.healthtracker.co.uk) that is currently being used in two EU FP7 projects—the Suicidality: Treatment Occurring in Paediatrics (STOP study; http://www.stop-study.com) and the Managing the Link and Strengthening Transition from Child to Adult Mental Health Care (MILESTONE) project (http://www.milestone-transitionstudy.eu). HealthTracker™ has also been used in a previous questionnaire development and validation study.^25^ The web-based questionnaires will follow the principles of data protection, security levels for health data, have an audit trail and Good Clinical Practice compliance. Participants will be given a unique ID number and log-in information, and will be asked to complete the questionnaires independently. All participants, including those with literacy issues, will have the option of going through the questionnaires over the phone with a member of the research team. Participants will also be able to complete paper versions of the questionnaires if requested. Questionnaire completion should not take longer than approximately 60 min for adults and 40 min for children.

Participant medical records will be accessed to validate the ACB against details of diagnoses obtained from patient case notes as well as against Development and Well-being Assessment (DAWBA^26^) diagnoses, IQ and treatment/medication status if they are available in case notes. Consent will be obtained to access medical notes. For children recruited via schools, the research team will also request details about IQ, educational attainment and diagnoses from school records. Parental consent will be obtained to do this. Where measures of IQ are not available from participant medical/school records, a brief measure of IQ will be collected by the research team (see table 1).

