##### Phase 2 recruitment

###### Main sample

Individuals with ASD (children, young people and adults) and their parents/caregivers/relatives/partners, teachers/employers and clinicians will be invited to take part (see below for inclusion criteria). Individuals with ASD will be recruited via clinician/researcher invite as well as via poster advertisements within healthcare and community settings, social media and websites for ASD support groups. Individuals with ASD will also be recruited from autism-specific schools and residential settings. Researchers will primarily be recruiting participants via clinics within participating trusts; the aim is to recruit approximately 75% via this method. This is to ensure access to medical notes for as many participants as possible. However, participants will not be excluded if they are not currently under the care of participating trusts. Parental consent will be obtained to request details about the child's IQ, educational attainment and diagnosis from school records.

Parents of children with ASD will be asked to provide details of their child's teacher and clinician, and will provide consent for the research team to contact them and invite them to complete the study questionnaires. Adults with ASD will be asked to provide details of another person who knows them well (either a parent/caregiver/relative/partner) who would be able to complete a questionnaire about them. Adults with ASD will also be asked to provide contact details for their clinician and their employer (if applicable and appropriate).

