##### Phase 2 sample size

###### Main sample

For this stage of the study, we will aim to recruit 200 people with ASD (approximately 100 adults and 100 children), in addition to their parent/carer/partner, teacher/employer and clinician, to complete the ACB and gold standard measures for analysis of reliability and validity of the ACB (see table 1). In a population cohort of people with ASD, the approximate IQ distribution was as follows: 15% had IQ<50, 40% had 50<IQ<70, 40% had an average IQ (70<IQ<115) and 5% had an above average IQ (IQ>115).^18^ We will aim to recruit across the spectrum of IQ in similar proportions to this population sample to provide a representation of a ‘typical’ ASD population, and ensure generalisability of findings. Attempts will be made to obtain estimates of IQ for individuals with ASD from school/medical notes. However, where this is not available, the research team will collect a brief measure of IQ through completing the Wechsler Abbreviated Scale of Intelligence^27^ during brief home visits to participant homes. All parents, caregivers, relatives and partners will be asked to provide an estimate of the cognitive functional age of the individual with ASD on their demographic questionnaire.

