##### Validity

Scale comparisons will be used to investigate the concurrent convergent validity of the ACB. Pearson correlation coefficients will be calculated to explore the association between ACB scores and other measures collected that are commonly used in clinical practice (table 1; subscale scores will be investigated where appropriate).

Receiver operating characteristic (ROC) analyses will be conducted to evaluate the discriminative power of the instrument. Currently, there is no existing gold-standard instrument for the identification of concerning behaviour in ASD. Therefore, ROC analyses will be conducted using scores from the Achenbach suite of measures (Child Behaviour Checklist;^28^ Youth Self-Report;^28^ Adult Behaviour Checklist;^29^ Adult Self-Report^29^), and the Aberrant Behaviour Checklist^30^ collected as part of the validation phase of this study (see table 1). Where data are available, ROC analyses will also be conducted according to the presence or absence of clinical and/or the structured DAWBA diagnosis taken from the patient's medical notes. For clinical cut-offs, we are able to estimate the ROC against the structured psychiatric assessment with a 95% CIs of ±0.12 (assuming a false-positive rate of 20% and true-positive rate of 28%^31^). In addition, independent samples t tests will be performed with grouping variable DAWBA and/or clinical diagnoses (coded 1 for positive and 0 for negative diagnosis) to assess differences in ACB scoring and the ability of the ACB to distinguish between different groups of patients.

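### The diagnosis-based ROC and t tests are not independent for the clinician-report ACB, because its rater will usually know the diagnosis it is tested against

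*Protocol article*

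**What the plan says.** **The criterion.** In the protocol article, the Phase 2 Main sample section states: "Participant medical records will be accessed to validate the ACB against details of diagnoses obtained from patient case notes". The Validity section then plans, where data are available, ROC analyses by "presence or absence of clinical and/or the structured DAWBA diagnosis taken from the patient's medical notes". It adds that "independent samples t tests will be performed with grouping variable DAWBA and/or clinical diagnoses", with the purpose "to assess differences in ACB scoring and the ability of the ACB to distinguish between different groups of patients". All of this is written for the ACB as a whole. No informant version is excepted and no masking is mentioned.

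**The rater.** Phase 2 sample size, Main sample, recruits 200 people with ASD "in addition to their parent/carer/partner, teacher/employer and clinician, to complete the ACB and gold standard measures". Phase 2 recruitment, Main sample, says how that clinician is found. For children: "Parents of children with ASD will be asked to provide details of their child's teacher and clinician". For adults: "Adults with ASD will also be asked to provide contact details for their clinician and their employer". Table 1 heads the corresponding column as clinician or researcher.

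**The other ROC references.** The Validity section names the Achenbach suite and the Aberrant Behaviour Checklist (ABC) first. Table 1 assigns these to people with ASD (Achenbach self-report forms only), parents, carers or partners, teachers and employers. None is assigned to the clinician.

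**The concern.** A discrimination analysis is informative when the index score is given without knowledge of the reference classification. Here the person scoring the clinician-report ACB is someone who ordinarily knows the reference. If that knowledge moves the score, part of the separation between diagnosed and undiagnosed participants reflects the rater's knowledge and not the instrument.

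Two features of the article make this matter. The Aim section presents the ACB as a screen for symptoms that may need fuller assessment, and a score from a rater who already knows the outcome of that assessment does not test screening. The Introduction also says that many clinicians lack confidence in recognising co-occurring conditions and that diagnostic overshadowing occurs. A clinician who puts anxiety down to ASD could both leave it out of the notes and score it low on the ACB. Two errors would then agree and count as a correct negative.

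At stake is the credibility of the diagnosis-based AUC and group difference for the clinician version, and any comparison of that figure with the other versions.

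**Working it through.** **Step 1: trace the pairing.**

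- *Who rates?* The participant's own clinician, named by the parent or by the adult participant (Phase 2 recruitment and Phase 2 sample size, both under Main sample).
- *What is the criterion?* A clinical or DAWBA diagnosis already in that participant's notes (Validity; Phase 2 Main sample).
- *How common is the pairing?* The article aims to recruit about 75% through participating trusts' clinics, precisely so that notes can be reached. A participant under a clinic's care with notes available is therefore the typical case.
- *Does anything separate rater from criterion?* Nothing in the Validity section does. A DAWBA diagnosis is more structured, but it is read from the same notes. Where a researcher rates instead, the research team also draws on the records, and no order of work is given.

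Rating and reference are therefore not independent for this version. That the clinician knows the diagnosis is close to unavoidable. That the clinician made it is possible but not stated.

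**Step 2: the stated precision.** The Validity section gives a 95% CI of ±0.12, assuming a false-positive rate of 20% and a true-positive rate of 28%. With the Wald half-width 1.96 × √(p(1−p)/n) = 0.12:

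- p = 0.28: n = 1.96² × 0.28 × 0.72 / 0.12² ≈ 54
- p = 0.20: n = 1.96² × 0.20 × 0.80 / 0.12² ≈ 43

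The number of participants expected to have a recorded diagnosis is not given, so ±0.12 cannot be fully reproduced. Either way it describes sampling error. A bias of the kind described here would not show in that interval, and a larger sample would not remove it.

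**Step 3: direction, by illustration.** Assume normal scores with equal variances, a true separation d (in SD), and a shift g added to the clinician's ratings of diagnosed patients because the diagnosis is known. Then AUC = Φ((d + g)/√2). Both d and g are assumptions; neither is in the documents.

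| True AUC (g = 0) | g = 0.3 | g = 0.5 | g = 0.8 |
|---|---|---|---|
| 0.70 | 0.77 | 0.81 | 0.86 |
| 0.71 (d = 0.8) | 0.78 | 0.82 | 0.87 |
| 0.80 | 0.85 | 0.88 | 0.92 |

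For the middle row: Φ(0.8/√2) = 0.714, Φ(1.1/√2) = 0.782, Φ(1.3/√2) = 0.821, Φ(1.6/√2) = 0.871. Any positive g raises the apparent AUC. The t test moves the same way, because the standardised group difference becomes d + g.

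**The case against.** The strongest reply is that this rests on silence: the Validity section does not say in terms that clinician scores enter the diagnosis-based analyses, and a condensed article may leave version-by-version detail and masking to a fuller document. That does not dispose of the point. The article fixes both the rater and the criterion and applies the analysis to the ACB without exception, so following it as written produces the non-independent figure.

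Other objections stand and limit the point:

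- **Other versions.** A reader might infer that only the clinician version is affected. The documents do not support that. Parents and adults with ASD report current treatment, so many may know the diagnoses. A milder form in their versions is plausible.
- **Unaffected analyses.** A reader might infer that the clinician version has no sound test of discrimination. In fact the ROC analyses against the Achenbach measures and the ABC rely on other raters and are already planned. The note-based ROC is an addition to them, where data allow.
- **The CGI.** It is the only other instrument that Table 1 gives the clinician or researcher, but sharing a rater with a comparator is not peculiar to this version. Self, parent, partner and teacher forms also have same-rater comparators.
- **Size.** A reader might take the d = 0.8 row as showing inflation of 0.07 to 0.16, comparable with ±0.12. The shifts are assumed, and the comparison sets an assumed bias against sampling precision.
- **Consequences.** Nothing in the article ties a recommendation of the clinician version to this AUC.

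**Conclusion.** The point holds in a limited form. As written, the note-based ROC and t tests for the clinician-report ACB compare a rating with a criterion that the rater will usually know and may have set. The result is not independent evidence of discrimination and is likely biased upward. The problem is probably strongest for this version, though it may not be confined to it.

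The amount cannot be determined from the documents; the table shows direction and possible scale under stated assumptions only. The conclusion rests on two premises: that a participant's own clinician ordinarily knows a diagnosis in that participant's notes, and that such knowledge tends to raise ratings of diagnosed patients. It does not require that the clinician made the diagnosis, or that the researcher who rates is the one who reads the notes; the article states neither.

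**What to change.** In the Validity section:

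1. Report the diagnosis-based ROC analyses and t tests separately by informant version.
2. Exclude the clinician version from them, or report it as descriptive and labelled not independent.
3. Base the clinician version's discrimination on measures already collected from others: the Achenbach self-report, parent/carer, partner, teacher and employer forms, and the ABC from parents, carers, partners, teachers and employers.
4. Where a researcher is the rater, have the ACB and CGI completed before diagnoses are extracted from the notes, where feasible. This may not fully mask the researcher, since contact with treating clinicians before consent and retrieval of IQ from records are both foreseen.

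Items 1 to 3 change analysis wording only and need no new data or participants. Item 4 is an order-of-work rule; formally separating the roles could need staff time. The downside is a less favourable, or absent, diagnosis-based figure for the clinician version.

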###### Factor analysis

To identify meaningful item clusters, exploratory factor analysis for ordinal data will be used for exploratory analyses of the item pool. If required (eg, in the case of Likert scales having fewer than five response options, substantial floor/ceiling effects, highly skewed items, data not missing at random), item factor analysis will be conducted in MPlus (latent trait model) to avoid biased parameter estimates.

## Ethics and dissemination

This study has received ethical approval from the NHS Research Ethics Committee: London-Camden and King's Cross (ref: 15/LO/0085) and is currently recruiting participants. The aim of the study is to develop and validate an instrument to assess mental health and concerning behaviour in ASD. The study output will provide a clinically relevant tool, predominantly for use with individuals with ASD. Future research will require the recruitment of a second sample of participants in order for Confirmatory Factor Analysis to be conducted on the proposed factor structure resulting from this study. It is also hoped the instrument will be effective as an outcome measure for use in ASD intervention research. If the instrument is found to be a valid measure of concerning behaviour in ASD, future research will also need to assess the sensitivity of the instrument to change following intervention in a randomised controlled trial. The findings of this study will be disseminated to healthcare professionals and scientists in the field through publication in peer-reviewed journals and conference presentations.
